#### Exploratory outcomes—Mood, anxiety, and health-related quality of life

Mood, anxiety, and health-related quality of life will be assessed using validated self-reported questionnaires provided through online forms. *Mood and anxiety* will be assessed using the 30-item Geriatric Depression Scale [49], the State Anxiety Inventory [50], the Perceived Stress Scale [51], the Perseverative Thinking Questionnaire [52], and Connor-Davidson Resilience Scale 10 [53]. *Health-related quality of life* will be measured using the 12-item Short Form Survey [54].

#### Other variables

Additional variables that might play a potential moderating role on trial outcome include *social activity and support* using the Social and Community Involvement Questionnaire [55] and the Lubben Social Network Scale [56], *sleep* using the Pittsburg Sleep Quality Index [57], and the Berlin Questionnaire [58], *diet* using the Short Diet Questionnaire [59], *cognitive reserve* using years of education and a modified version of the Rami and colleagues’ cognitive reserve questionnaire [60] adapted for French and English by the CIMA-Q team [61], *prior physical activity* using the Physical Activity Scale for the Elderly [62], *anxiety-traits* using Anxiety Sensitivity Index [63], Intolerance to Uncertainty Scale [64], Perceived Vulnerability to Disease [65] and Trait Anxiety Inventory [50], and *gender* using the Bem Sex-Role Inventory [66]. Additionally, the level of *participants’ satisfaction* regarding their evaluations and training will be assessed by a dedicated questionnaire after the 6-month evaluations. These scales will be used as covariables to take into account aspects related to motivation. All self-reported scales and questionnaires will be performed using online forms as described in Table 1.

### Randomization and blinding

All participants who provide their consent, fulfill the inclusion criteria, and complete the baseline assessment will be randomized. Randomization will be performed by a naive staff member who is not involved in any other aspect of the COVEPIC study, upon request of the recruitment coordinator. The staff member will assign the participant to one of the two interventions according to simple randomization with a 1:1 allocation ratio. The Montreal Health Innovations Coordinating Center (MHICC), a research organization independent from the present study team, will generate the randomization sequence (i.e., computer-generated random numbers) that will be protected in a locked sheet. Participants’ intervention group will then be shared to the research staff in charge of training. No modification of group allocation will be allowed. This clinical trial is a single-blinded study. Research personnel performing the outcome assessments at baseline, three, six, and twelve months will be blinded to group allocation. Participants will be aware of the type of training they receive.

### Data analysis

#### Sample size calculation

The Montreal Health Innovations Coordinating Center**’**s biostatistics team completed the sample size calculation. The calculation was based on values available in the literature for physical exercise training alone [67], on different plausible values for the combined physical and cognitive training (since there are no values in the literature for this group), and on clinically relevant effect sizes to detect the cognitive outcome. A sample size of 49 subjects in each group will have 80% power to detect a difference in means of **−** 0.186 (the difference between a physical training alone mean of 0.239 and a combined training mean of 0.425, for an effect size of 0.624), assuming that the common standard deviation is 0.298 using a two-group *t* test with a 0.050 two-sided significance level. Considering a 20% attrition rate observed in our previous exercise studies, 61 participants will be recruited per intervention arm to ensure the targeted 49 participants per group (61 * .80 = 49) for a total of 122 participants.

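### The sample-size statement does not reproduce: its own inputs give 86.4% power at 49 per group, and 80% power needs only 42 per group

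*Protocol article*

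**What the plan says.** The Sample size calculation section of the protocol article gives a complete specification.

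- Size, power and difference: "A sample size of 49 subjects in each group will have 80% power to detect a difference in means of" 0.186 in absolute value, described as "the difference between a physical training alone mean of 0.239 and a combined training mean of 0.425".
- Standardised effect and spread: "for an effect size of 0.624", "assuming that the common standard deviation is 0.298".
- Test: a two-group t "test with a 0.050 two-sided significance level".

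The Randomization and blinding section fixes equal groups: "simple randomization with a 1:1 allocation ratio".

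The 49 is then treated as the number of completers to secure in each group. With 20% attrition it becomes 61 recruited per arm and 122 in total.

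**The concern.** Difference, standard deviation, significance level, test, allocation, n and power are all printed, so the statement can be checked without any outside figure. For a two-sample t test, any one of these quantities follows from the others. Here the stated n is not the n that the other figures yield, and the stated power is not the power that the stated n yields.

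The enrolment target of 122 rests on this paragraph. As printed, a reader cannot tell whether the trial has a margin of about six points of power over its nominal 80%, or whether there is no margin and one of the design assumptions has been reported wrongly.

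**Working it through.** **Inputs**, all from the Sample size calculation section except the 1:1 allocation: means 0.239 and 0.425; SD 0.298; two-sided alpha 0.05; two-group t test; n = 49 per group; power 80%; attrition 20%.

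**Step 1. Effect size.** 0.425 − 0.239 = 0.186, and d = 0.186/0.298 = 0.6242. The printed 0.624 reproduces.

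**Step 2. Power at 49 per group.** The t statistic has 2n − 2 degrees of freedom and noncentrality d × √(n/2). Power is the probability that its absolute value exceeds the two-sided 5% critical value.

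| n per group | df | critical t | d × √(n/2) | power |
|---|---|---|---|---|
| 41 | 80 | 1.990 | 2.826 | 79.7% |
| 42 | 82 | 1.989 | 2.860 | 80.7% |
| 48 | 94 | 1.986 | 3.058 | 85.7% |
| 49 | 96 | 1.985 | 3.089 | **86.4%** |

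A simulation of 200,000 trials with these means and this SD also gave 86.4%. The normal approximation gives Φ(3.089 − 1.960) = 87.1%. The stated 80% does not reproduce.

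**Step 3. n for 80% power.** The normal approximation is 2 × (1.960 + 0.842)²/0.6242² = 40.3, rounded up to 41. The exact t solution is 41.28, rounded up to **42**. The stated 49 does not reproduce either. It is not the answer for a neighbouring power: 85% needs 48 and 90% needs 55.

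**Step 4. Recruitment.** 42/0.80 = 52.5, so 53 per arm and 106 in total, against the planned 61 and 122.

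**Step 5. Could rounding explain it?** The two means are printed to three decimals, so the difference could lie between 0.185 and 0.187, and the SD between 0.2975 and 0.2985. Across that range, power at 49 per group stays between 85.9% and 86.9%, and the n for 80% stays at 41 or 42.

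**Step 6. Could a different test explain it?** A one-sided 0.05 test moves away from 49: it needs 33 per group, and 49 would have 92.3%. Inflation for a rank test gives 44 (relative efficiency 0.955) or 48 (efficiency 0.864, or a flat 15% inflation). Neither is 49, and the section names a t test.

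**Step 7. What would make 49 right for 80%?** Solving for d at n = 49 gives 0.572. That is a difference of 0.572 × 0.298 = 0.170 at the stated SD, or an SD of 0.186/0.572 = 0.325 at the stated difference.

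**The case against.** The strongest defence is that the discrepancy is harmless. With the inputs as printed, the trial plans more participants than 80% power requires. None of the tests under Planned data analysis depends on the 80% figure. If the sentence is read as *at least 80%*, it is not false. Most of this stands: the matter is one of reporting, and no analysis is put at risk. What does not stand is the arithmetic. Even on the generous reading, 49 is not the number these inputs produce, and the section treats it as the target on which enrolment is built.

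A reader might be tempted to go further in four ways, none of which the document supports.

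- *The trial is underpowered.* Under the stated inputs it has more power than claimed. If the SD were really 0.325, power at 49 would be the claimed 80%, so that slip would not mean a shortfall against the claim.
- *A halved alpha was used.* Two-sided 0.025 gives 79.0% at 49 and needs 51 by the exact t test. It is close, but it contradicts the printed 0.050 and remains a guess. So does attrition counted twice (41 × 1.2 = 49.2).
- *The surplus can pay for multiplicity control.* Halving alpha already brings power just under 80%. Splitting it over the four primary cognitive measures (alpha 0.0125) leaves 70.6%.
- *The plan needs 62 per arm.* 61 × 0.80 = 48.8, which is 49 within rounding, and 48 per group would still have 85.7%.

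**Conclusion.** Wrong as written. With a difference of 0.186, an SD of 0.298, a two-sided 0.050 level and a two-group t test, 49 per group has 86.4% power, 6.4 points above the stated 80%. Power of 80% needs 42 per group, 7 fewer than stated. Rounding and the adjustments named in the section (none before the attrition step) do not account for the gap.

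The n, the power or at least one input is therefore misstated. The document does not show which. Because 0.186, 0.298 and 0.624 agree with one another, a slip in the SD alone would have had to carry through to the effect size as well.

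The conclusion assumes the standard equal-variance t test with equal groups of 49 completers. If the printed difference, SD and alpha are correct, the error is in the safe direction.

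**What to change.** Retrieve the coordinating centre's original calculation, re-run it and restate the paragraph in one of two ways.

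1. If the difference, SD and alpha are as printed, keep 61 per arm and state about 86% power for an effect size of 0.624 with 49 completers per group. Equivalently, state 80% power for an effect size of 0.572, which is a difference of 0.170 at SD 0.298.
2. If 49 and 80% came correctly from the software, correct the input that was mis-transcribed, and the effect size with it if the difference or SD changes.

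The cost is one corrected paragraph. Enrolment, design and analysis do not change.

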#### Planned data analysis

The variables in the study will be presented using descriptive statistics. The mean, standard deviation, median, minimum, Q1, Q3, and maximum will be presented for continuous variables. The number and percentage will be presented for nominal/ordinal variables. The statistical tests' assumptions will be examined, and data transformation or non-parametric analyses may be used as appropriate. SPSS and SAS version 9.4 or higher software will be used to conduct the analyses. Statistical tests will be two-tailed, and a *p* value of less than 0.05 will be considered as the indication of statistical significance.

Mean changes in cognitive performance from baseline will be analyzed using a repeated measures analysis of covariance (ANCOVA) model, adjusted for age, sex, education, and the dose of physical exercise, including the effects of the intervention (physical exercise alone or combined with cognitive training) and time (pre at baseline, mid at 3 months, post-intervention at 6 months). Observation of a statistically significant difference in the primary outcome between pre- and post-intervention timepoints will be considered as the evidence of the intervention's efficacy (i.e., primary hypothesis). The interaction between intervention arms (i.e., physical exercise alone or combined with cognitive training) and performance changes from pre to post-intervention will address the added value of the cognitive training compared to physical exercise alone (i.e., secondary hypothesis). Observation of a statistically significant *intervention × time* interaction in the primary outcome will be considered as the evidence that the differential effect operates by the exercises and combined interventions. Secondary and exploratory outcomes will be analyzed as the primary outcome.

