## Study limitation and development perspectives

Despite its strengths mentioned above, the proposed design presents some limitations. Due to this exceptional pandemic context, some ethical considerations refrained the research team from implementing a control group. Nevertheless, to address this limitation, at least partially, all participants will be included in the final analyses, without exclusion based on participation, to document the dose-response relationship between physical exercise and outcome effects. Additionally, sex was not taken into account in recruitment and randomization processes, although sex differences have been reported on cognition [74], as well as in exercise-training effects on cognition in healthy older adults [75]. Consequently, sex will be considered as a covariate in all statistical analyses. Also, a recent study from Peterman et al. [76] highlights that longitudinal changes in nonexercise prediction equations of cardiorespiratory fitness were associated with changes in cardiorespiratory fitness as measured by standardized VO2_max_ protocols but present significant errors in their predictions. Therefore, the use of nonexercise prediction equations could lead to a significant error in the estimated change of participants' cardiorespiratory fitness.

Future studies using more direct physical fitness assessments and tracking devices for remote monitoring could help better inform on the effect of physical exercise training in seniors. Indeed, adding a direct measure of physical fitness could help inform on participants' physical condition when they engage themselves in the intervention, as well as their progression. Its combination with a measurement of frequency, duration, and intensity of physical exercise sessions provided by tracking devices such as smartwatches or smart garments may shed light on the relationship between exercise training characteristics and the changes in physical fitness over the course of the intervention. This kind of information may substantially improve remote monitoring, helping the training coaches provide resources and recommendations adapted to each participant according to their physical fitness and progression.

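### The between-arm analysis has an unclear response, no adjustment for the baseline score, and two unreconciled decision rules, one of which a difference present only at 3 months could satisfy

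*Protocol article*

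**What the plan says.** In the protocol article, Planned data analysis, the response is described thus: "Mean changes in cognitive performance from baseline will be analyzed using a repeated measures analysis of covariance (ANCOVA) model". The model contains the intervention and "time (pre at baseline, mid at 3 months, post-intervention at 6 months"), and is adjusted for age, sex, education and the dose of physical exercise. The baseline score is not a listed covariate. Dose-Response exploration repeats the three-level time factor.

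The same section sets the decision rules. A pre-to-post difference in the primary outcome is the evidence for the primary hypothesis. For the secondary hypothesis, the added value of cognitive training, one sentence points to the interaction of arm with the change from pre- to post-intervention. The next says that a significant intervention by time "interaction in the primary outcome will be considered as the evidence that the differential effect operates" by the two interventions.

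Sample size calculation sizes the trial on a single two-group comparison: "A sample size of 49 subjects in each group will have 80% power to detect a difference in means of" a given size, here 0.186 in absolute value. That size is described as "the difference between a physical training alone mean of 0.239 and a combined training mean of 0.425, for an effect size of 0.624". The comparison is a t test "with a 0.050 two-sided significance level", and the calculation proceeds by "assuming that the common standard deviation is 0.298". Randomization and blinding requires a completed baseline assessment before randomisation.

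**The concern.** Three things do not fit together.

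- **Response.** A change from baseline cannot be a response at the baseline visit, since every participant's value there is zero. If raw scores are meant, the model can be fitted, but the text should say so.
- **Baseline score.** With raw scores at three times and no use of the baseline score beyond that, the arm by time term compares unadjusted change scores. Under randomisation this is valid, but less precise than an analysis that adjusts for baseline or constrains the arms to share a baseline mean.
- **Decision rule.** The between-arm hypothesis concerns the post-intervention difference, and the sample size rests on one contrast. A significant interaction over three time levels shows only that the arms' profiles differ somewhere. A benefit seen at 3 months and lost by 6 months would count as evidence under the second sentence but not under the first. With both rules in print, the choice could be made after the data are seen.

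**Working it through.** **Inputs from the article:** means 0.239 and 0.425, SD 0.298, two-sided alpha 0.05, 49 per arm, 20% attrition, 61 per arm.

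**Assumptions:** 0.298 is the SD of the 6-month change (the article does not say whether it is that or the SD of a score); equal variances over time; compound symmetry for the 2-df test; correlation rho between the baseline and 6-month scores, given the other covariates, of 0.6 to 0.8.

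**1. The plan's own figure.** Difference 0.425 − 0.239 = 0.186; effect size 0.186/0.298 = 0.624, as stated. The exact two-group t test needs 42 per arm for 80% power (80.7% at 42, 79.7% at 41). At 49 per arm, power is 86.4%. The stated 49 is therefore conservative for the stated inputs, and 86.4% is the right reference for what follows.

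**2. Effect of using the baseline score.** With score variance s²:
- change score: variance 2s²(1 − rho)
- baseline-adjusted score: variance s²(1 − rho²)
- ratio: (1 − rho²) / [2(1 − rho)] = (1 + rho)/2

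The effect size becomes 0.624/√ratio. At 49 per arm:

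| rho (assumed) | variance ratio | effect size | power |
|---|---|---|---|
| unadjusted change | 1 | 0.624 | 86.4% |
| 0.8 | 0.90 | 0.658 | 89.7% |
| 0.7 | 0.85 | 0.677 | 91.3% |
| 0.6 | 0.80 | 0.698 | 92.8% |

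**3. The 1-df contrast against the 2-df interaction.** At n = 49 per arm, with no baseline adjustment:
- 1 df: noncentrality (n/2) × 0.186²/0.298² = 24.5 × 0.034596/0.088804 = 9.54; power 86.4%.
- 2 df: noncentrality (n/2) × SS/(0.298²/2), where SS is the sum of squared deviations of the three arm differences from their mean.

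| Arm difference at 0, 3, 6 months (as a fraction of 0.186) | SS/0.186² | noncentrality | 2-df power |
|---|---|---|---|
| 0, 0.5, 1 (linear) | 0.500 | 9.54 | 78–79% |
| 0, 0.75, 1 | 0.542 | 10.34 | about 82% |
| 0, 0, 1 or 0, 1, 1 | 0.667 | 12.73 | 89–90% |
| 0, 1, 0 (gone by 6 months) | 0.667 | 12.73 | 89–90% |

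The ranges cover the univariate and multivariate forms of the test. For a linear course both tests have noncentrality 9.54, but the interaction spreads it over 2 df and loses 7 to 8 points. If the difference is nil or already full at 3 months, nothing is lost. The last row matters most: a difference that exists only at 3 months would be declared evidence about nine times in ten, whereas the 6-month contrast would reject at its 5% level.

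**The case against.** The reply has several parts, and some of it stands.

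- **The 6-month contrast is already there.** The sentence before the interaction rule names the arm by pre-to-post change, and the rule can be read as shorthand for it. That is a fair reading, so the fault is two rules not reconciled, not a missing contrast.
- **Unadjusted change is valid, and baseline belongs in the time factor because the primary hypothesis is a pre-post difference.** Both are true. Adjustment is about precision, and its size rests on an assumed correlation. It costs no data, because every randomised participant has a baseline assessment.
- **Power is not shown to fall short.** Leaving out baseline adjustment keeps power at 86.4% under the stated inputs. Only the 2-df rule goes below 80%, only slightly, and only for courses near linear.

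A reader might also infer from the model's name that anyone with a missed visit is dropped, that about 24 of 122 (0.20 × 122 = 24.4) would be discarded, that this biases the results, and that it contradicts the statement that "all participants will be included in the final analyses, without exclusion based on participation". The documents do not support this. The article names SPSS and SAS but no procedure and no missing-data rule. Both packages can fit likelihood-based models that keep partial data, and such detail may sit in an analysis plan not shown. The 20% is a recruitment allowance, not an exclusion rule, and nothing says who would be lost. The quoted statement concerns the degree of participation, in support of the dose-response work.

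**Conclusion.** The point holds in a limited form. The response and the time factor are inconsistent as worded, the baseline score is left unused as an adjustment, and one hypothesis has two decision rules that can disagree. The main harm is the mismatch between test and question: the interaction rule can be met without any 6-month difference.

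The cost in power is moderate. Adjustment would move about 86% to 90–93% for rho 0.8 to 0.6, and the omnibus test would have about 79% under a linear course. If 0.298 is the SD of a single score, the SD of change is 0.298 × √(2(1 − rho)) and all these powers shift; the variance ratio does not. No claim is made that participants are excluded or that the results would be biased.

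**What to change.** 1. State that the response is the raw score, not the change.
2. Fit a constrained longitudinal mixed model to the scores at baseline, 3 and 6 months, with a common baseline mean across arms. For the arm comparison alone, a mixed model of the 3- and 6-month scores adjusted for the baseline score is an alternative.
3. Declare the arm difference at 6 months the single 1-df test of the between-arm (secondary) hypothesis, and report the 3-month difference and the omnibus interaction as descriptive.
4. Keep the pre-to-6-month contrast as the test of the declared primary hypothesis. The constrained model gives it directly; the model with only 3- and 6-month responses does not, so that option needs a separate analysis for it.

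The cost is wording and a choice of procedure in software already named, with no new data. Fitting by likelihood also keeps participants with partial data, at the small price of assuming that data are missing at random; a sensitivity analysis to that assumption would be a sensible companion. The remaining covariates are not part of this point.

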### Interventions

After being randomly (see the “Randomization and blinding” section) assigned to one of the 2 study arms, participants will receive a group-specific training guide. The training guide contains recommendations about the nature, intensity, and frequency of the training sessions. Participants will then attend an introductory session over the phone given by their training coach. Participants will be invited to follow the training guide while adjusting their dose as they see fit.

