#### Physical exercise and cognitive training

The combined multidomain intervention will include home-based physical exercise and cognitive training. Home-based physical exercise will be exactly similar to the conditions described in the previous section. Due to the important variations observed in the short-term effect of exercise on cognitive performances [31], home-based cognitive training will either take place prior to the exercise session or at least 3 h post-exercise training. Participants will be asked to complete their cognitive training in a quiet and comfortable setting without distraction. Both validated computerized cognitive tasks and video capsules will be provided to the participants. Participants will be encouraged to perform at least three sessions per week (30 min/session): two sessions of computerized cognitive tasks and the other one dedicated to the video capsules.

For the computerized cognitive training sessions, the following three tasks will be available: (1) dual-task training that requires participants to maintain and prepare for many response alternatives and to share attention between two concurrent tasks (i.e., Dual-task [32]), (2) inhibition training, which requires the participants to refrain from giving an automatic response (i.e., Stroop task [33]), and (3) working memory training, which asks participants to maintain and update information in working memory to recall items presented earlier (i.e., N-Back task [34]). Each cognitive task lasts approximately 15 min possesses its respective sets of visual stimuli (e.g., letters, numbers, symbols) and matching button symbols. Participants will be instructed to perform the tasks as fast as possible while maintaining accuracy. The three tasks will be presented in a fixed order for all the participants. The level of difficulty of each cognitive task will be gradually increased over the course of the participant’s cognitive training to avoid cognitive task automatization and to maintain stimulation [35]. These computerized tasks will also include visual feedback as well as a histogram of daily performances to encourage improvement and maintain motivation.

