##### Dose-Response exploration

The type of activity, its frequency, duration, and intensity (i.e., according to the Borg scale) will be considered to compute the dose of physical exercise. The weekly dose of physical exercise will be converted in kcal and in METs using the Compendium of Physical Activities (i.e., coding scheme classifying specific physical activities by their rate of energy expenditure) [68, 69]. The effect of physical exercise dose on cognitive and physical functions will be evaluated according to participants’ mean weekly dose during the 6 months of intervention. Based on the overall study sample distribution, participants will be classified into three groups: higher, medium, and lower doses of physical exercise (i.e., tercile split). How the dose of physical exercise affects the primary and the secondary outcomes will be addressed by a repeated measures ANCOVA model, adjusted for age, sex, and education, including the effects of the intervention (physical exercise alone or combined with cognitive training), time (pre at baseline, mid at 3 months, post-intervention at 6 months) and dose groups (lower, medium or higher doses). An exploration of the dose-response effect for cognitive training will also be performed within the combined physical exercise and cognitive training intervention group. The dose of cognitive training will be considered according to its mean weekly duration. How the dose of cognitive training affects the primary and the secondary outcomes will be addressed by a repeated measures ANCOVA model, adjusted for age, sex, education, and the dose of physical exercise, including the effects of time (pre at baseline, mid at 3 months, post-intervention at 6 months) and dose groups (lower or higher doses of cognitive training; median split).

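### The model for the randomised arm comparison adjusts for exercise dose achieved after randomisation, which can bias the arm-by-time estimate in either direction

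*Protocol article*

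**What the plan says.** Under Planned data analysis, the protocol article analyses mean change in cognition with a repeated measures ANCOVA "adjusted for age, sex, education, and the dose of physical exercise, including the effects of the intervention" and time, where time has three levels: baseline, 3 months and 6 months. The intervention-by-time interaction from this model is the evidence for adding cognitive training. The protocol labels that the secondary hypothesis; the primary one is the pre-post change. Secondary and exploratory outcomes are handled the same way. No arm comparison without dose is described.

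Dose-Response exploration defines dose from sessions performed ("The type of activity, its frequency, duration, and intensity") and evaluates it as the "mean weekly dose during the 6 months of intervention". No baseline version of this variable is defined; prior activity is a separate questionnaire.

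Under Interventions: "Participants will be invited to follow the training guide while adjusting their dose as they see fit". Remote monitoring and counseling has coaches adapting their recommendations each week to the reported dose, and Randomization and blinding says that training staff are told the allocation. In the combined arm only, "Participants will be encouraged to perform at least three sessions per week (30 min/session"), and this training "will either take place prior to the exercise session or at least 3 h post-exercise training".

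Other variables adds that satisfaction is measured after the 6-month evaluations, and continues: "These scales will be used as covariables to take into account aspects related to motivation". It names no model.

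**The concern.** Achieved dose arises after randomisation and over the same period as the outcome. The arm can move it: the combined arm has a further 3 × 30 = 90 minutes a week to fit in, with timing tied to exercise, and both participants and coaches know the allocation.

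Two things can follow when the arm contrast is conditioned on such a variable. First, any part of the effect of allocation that runs through exercise is removed, so the estimate is no longer the total effect of adding cognitive training. Second, motivation and health plausibly drive both dose and cognitive change. Comparing arms at equal dose then compares people who differ on those factors, even if dose itself has no effect. Randomisation no longer protects the comparison, and the other outcomes inherit the same model.

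**Working it through.** **Inputs from Sample size calculation:** 49 per arm, SD 0.298, means 0.239 and 0.425, two-sided alpha 0.05.

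**Assumed inputs (the document gives no figures):** the arms differ in dose by *a* SD (combined minus exercise alone), with |*a*| = 0, 0.2 or 0.5. An unmeasured factor explains half of the dose variance (loading √0.5 = 0.707) and has an effect *h* = 0.3 or 0.5 SD on cognitive change. Neither arm nor dose has any true effect.

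**Step 1, the plan's own figures.** 0.425 − 0.239 = 0.186 and 0.186 / 0.298 = 0.624, as stated. An exact t test reaches 80% power at 42 per arm, and 49 gives 86.4%. That mismatch is a separate matter, errs on the safe side and does not bear on this point.

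**Step 2, bias with change as the response and dose as a covariate.**

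Bias = −*a* × 0.707 × *h* × 0.298.

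Standard error of the arm coefficient in SD units = √[(1 − 0.5*h*²) × (2/49) × (1 + *a*²/4)]. Type I error follows from the non-central t distribution on 95 degrees of freedom.

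Example, *a* = −0.5 and *h* = 0.5: the bias is 0.5 × 0.707 × 0.5 = 0.177 SD, or 0.177 × 0.298 = 0.053 z. The standard error is √(0.875 × 0.0408 × 1.0625) = 0.195. The ratio is 0.907, and the type I error is 14.6%.

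| Dose difference | *h* | Size of bias (z) | Type I error |
|---|---|---|---|
| 0 | 0.3 or 0.5 | 0 | 5.0% |
| 0.2 SD | 0.3 | 0.013 | 5.5% |
| 0.2 SD | 0.5 | 0.021 | 6.6% |
| 0.5 SD | 0.3 | 0.032 | 8.1% |
| 0.5 SD | 0.5 | 0.053 | 14.6% |

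Against the 0.186 target, the last two rows are 0.032 / 0.186 = 17% and 0.053 / 0.186 = 28%. The bias favours the combined arm if that arm exercises less, and goes against it if it exercises more. Simulations of the same setting agree within their error: about 5 to 7% at 0.2 SD and 8 to 16% at 0.5 SD. Without dose in the model the bias is zero and the type I error about 5%.

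**Step 3, the change of target.** Suppose instead that dose truly affects cognition by 0.3 SD per SD and there is no shared cause. At a 0.5 SD dose difference, adjustment moves the estimate by 0.5 × 0.3 × 0.298 = 0.045. A total effect of 0.186 becomes 0.186 + 0.045 = 0.231 if the combined arm exercises less, or 0.186 − 0.045 = 0.141 if it exercises more (simulated: 0.229 and 0.142).

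**Step 4, how dose enters the model.** Let M be a person's mean dose. If dose contributes δM at every visit, the 6-month minus baseline contrast cancels it: δM − δM = 0. If it contributes δ₀M at baseline and δ₆M at 6 months, the contrast keeps (δ₆ − δ₀)M, and the result is that of Step 2. A numerical check on complete three-visit data confirmed this. Adding dose as a main effect left the arm-by-time coefficient unchanged to rounding, under both compound-symmetric and unstructured covariance. Adding dose-by-time changed it.

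**The case against.** The strongest objection is Step 4. The protocol lists dose among the adjusters, states no dose-by-time term, and gives time three levels including baseline. Read that way, with complete data, the arm-by-time estimate is untouched. This stands as a limit on the claim, but it does not clear the plan. The same sentence names mean change from baseline as what is analysed, which points to change scores, and the text does not settle which model is meant. Complete data are also unlikely when the protocol itself allows for 20% attrition.

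Second, the arms may not differ in dose. The exercise programme, its weekly target and the coaching calls are described as the same for both. With no difference there is no bias, and at 0.2 SD it is small. That also stands: the 0.5 SD case is an assumption. But the difference cannot be known in advance, and the protocol gives several routes by which it could arise.

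Third, the limitations section presents dose-response as partial compensation for having no control group. That supports the separate exploratory analysis. It does not support putting dose into the one comparison that randomisation protects.

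A reader might also infer that satisfaction is a term of this model. The documents do not say so: it is absent from the covariate list, the sentence about scales is ambiguous, and no model is named.

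**Conclusion.** The point holds as a conditional one. A covariate measured after randomisation sits in the model for the arm-by-time comparison, and no version without it is described. It can bias that comparison in either direction and replace the total randomised effect with an effect at equal dose. This requires that the arms differ in dose, and that change scores are the response or dose-by-time is fitted.

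Under the assumed shared cause and no true effect, the size runs from nothing (no dose difference), through about 0.01 to 0.02 z with type I error of about 5 to 7% (0.2 SD), to about 0.03 to 0.05 z with about 8 to 16% (0.5 SD).

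A reader might conclude that the estimate is certainly biased and that the type I error cannot be 5%. The documents do not support that, because they fix neither the dose difference nor how dose enters. Nor is this the test of the primary hypothesis: it is the primary-outcome model, used here for what the protocol calls the secondary hypothesis.

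**What to change.** Remove achieved exercise dose from every model that compares the arms, for primary, secondary and exploratory outcomes. Adjust only for baseline variables: age, sex and education. Treat the baseline outcome score in one of two ways, not both: as a level of the repeated response, as now written, or as a covariate in a model restricted to the 3- and 6-month responses. State which.

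Keep dose in the separate dose-response analysis, labelled exploratory. Add one sentence saying that satisfaction, measured after the 6-month evaluations, will not enter any arm-comparison model.

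The cost is wording in the protocol or analysis plan. No data are lost and no procedure changes. It should be settled before results by arm are seen.
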